## Abstract

**Background:**

Mental disorders are common during the peripartum period and may have far-reaching consequences for both mother and child. Unfortunately, most antenatal care systems do not provide any structured screening for maternal mental health. As a consequence, mental illnesses are often overlooked and not treated adequately. If correctly diagnosed, cognitive behavioral therapy is currently the treatment of choice for mental illnesses. In addition, mindfulness-based interventions (MBIs) seem to represent a promising treatment option for anxiety and depression during the peripartum period. Considering the internet’s increasing omnipresence, MBIs can also be offered electronically via a (tablet) computer or smartphone (electronically based MBI = eMBI).

**Objective:**

The current study aims to examine the clinical effectiveness and cost-effectiveness of an eMBI (the *mindmom* application) developed by an interdisciplinary team of gynecologists, psychologists, and midwives, teaching pregnant women how to deal with stress, pregnancy-related anxiety, and depressive symptoms. The study sample consists of pregnant women in their third trimester who screened positive for emotional distress. The *mindmom* study is a bicentric prospective randomized controlled trial (RCT), which is currently conducted at the University women’s hospitals of Heidelberg and Tübingen, Germany.

**Methods:**

Within the scope of the routine prenatal care, pregnant women attending routine pregnancy care in Baden-Wuerttemberg, Germany, are invited to participate in a screening for mental distress based on the Edinburgh Postnatal Depression Scale (EPDS). Women with an EPDS screening result > 9 will be referred to one of the *mindmom* coordinating study centers and are offered counseling either face-to-face or via videotelephony. After an initial psychological counseling, women are invited to participate in an eMBI in their last pregnancy trimester. The study will enroll *N* = 280 study participants (*N* = 140 per group), who are randomized 1:1 into the intervention (IG) or control group (treatment as usual = TAU).

All participants are requested to complete a total of 7 digital assessments (5 visits pre- and 2 follow-up visits postpartum), involving self-report questionnaires, sociodemographic and medical data, physiological measures, and morning cortisol profiles. The primary outcome will be depressive and anxiety symptoms, measured by the Edinburgh Postnatal Depression Scale, the State Trait Anxiety Questionnaire, and the Pregnancy-Related Anxiety Questionnaire. Secondary outcomes include mindfulness, satisfaction with birth, quality of life, fetal attachment, bonding, mode of delivery, and cost-effectiveness.

**Discussion:**

This is the first German RCT to examine the (cost-)effectiveness of an eMBI on maternal mental health during pregnancy. If successful, the *mindmom* app represents a low-threshold and cost-effective help for psychologically distressed women during pregnancy, thereby reducing the negative impact on perinatal health outcome.

**Trial registration:**

Deutsches Register Klinischer Studien, German Clinical Trials Register DRKS00017210. Registered on 13 January 2020. Retrospectively registered.

**Supplementary information:**

The online version contains supplementary material available at 10.1186/s13063-020-04873-3.

## Background

Mental disorders, especially anxiety and depressive disorders, are common during the peripartum period and may have far-reaching consequences for both mother and child [1–3]. The prevalence of peripartum depressive disorders is reported to be approximately 9% in Germany [4]. With prevalence rates ranging between 39% ante- and 16.5% postnatally, most studies indicate that women are even more susceptible to anxiety disorders during pregnancy [2, 3]. Furthermore, anxiety and depression have a very high comorbidity of approximately 50% [5].

Maternal psychological distress has been linked to adverse peripartum health outcomes for both mother and child, such as preterm delivery, low birth weight, maternal substance abuse in pregnancy, impaired mother-child interaction, childhood regulatory dysfunction, and impaired cognitive and psychomotor development [3, 6, 7].

Furthermore, the rising rate of cesarean delivery, which is currently estimated at 31% in Germany, is known to be associated with maternal mental disorders [4]. About 80% of indications for cesarean section are relative indications, of which 10% are due to increased levels of maternal anxiety. Effective treatment of peripartum psychological distress could thus have the potential to lower the cesarean section rate [8].

As most antenatal care systems worldwide do not provide any structured screening for maternal mental health, mental illnesses are often overlooked and not treated adequately. Recent studies have shown that peripartum depression is not detected in 80% of women, and only 20% of those affected receive an appropriate treatment [9]. This appears even more relevant, as maternal mood disorders can lead to substantial health care and societal costs. Furthermore, the treatment of peripartum mental disorders is particularly challenging, as medical treatment is often rejected for fear of harming the fetus [10, 11]. Thus, there is a high demand for integrating a validated screening for maternal mental distress in routine antenatal care and for easily accessible non-medical treatment options during pregnancy.

### Physiology of stress and neurobiological correlates

The high vulnerability for experiencing mental distress during the peripartum period can partly be attributed to the hormonal changes accompanying pregnancy and birth. Studies have repeatedly discussed associations with prolactin, gonadotropins, steroids, thyroid-stimulating hormone, and cortisol [2, 3]. One promising explanation is that mental disorders such as depression and anxiety are linked to changes in hypothalamic-pituitary-adrenocortical axis (HPAA) activity. In a current review, Szpunar and Parry identified significant correlations between morning cortisol levels and the presence of major depression [2, 3]. Furthermore, women with depressive and/or comorbid anxiety disorders during pregnancy respond to stress with a significantly higher cortisol release than healthy controls [12, 13].

During pregnancy, fetal cortisol concentrations are linearly associated with maternal blood concentrations [14, 15]. Thus, authors of the so-called fetal programming hypothesis postulated that elevated cortisol levels during pregnancy could possibly have continuing aftermath on the fetal environment through structural changes in the limbic system (e.g., hippocampus or amygdala) as well as in limbic regions of the cortex [16, 17]. Further studies on the predictive significance of daily maternal cortisol profile curves for the course of pregnancy and childhood development are urgently needed.

### Mindfulness-based interventions

Currently, cognitive behavioral therapy represents the treatment of choice for mental illnesses [18, 19]. During the past years, mindfulness-based interventions (MBIs) have increasingly become a focus of interest due to their efficacy and low costs and low-threshold access for everyone. By combining elements of established cognitive behavioral therapy and psychoeducational content, MBIs aim to reduce stress-related symptoms and support a self-effective approach to improve mental and physical well-being [20]. MBIs are not only suitable for stress management, but can also be applied in clinical settings [15, 21]. In a comprehensive meta-analysis examining 12,145 patients with different psychological disorders, MBIs were at least as effective as cognitive behavioral therapy or pharmacological therapy [21]. Furthermore, MBIs have been shown to be most effective in patients with symptoms of depression and anxiety [22] and appear to be at least equivalent, if not superior, to classical psychotherapy in reducing depressive symptoms [23]. Various smaller studies demonstrate that MBIs also present a promising means of reducing anxiety and depression during the peripartum period [3, 24]. Apart from that, practicing MBIs may also positively influence physiological changes such as decrease of circulatory inflammatory proteins and reduction of cortisol response to stressors [25].

Considering the increasing omnipresence of the internet, MBI can also be offered electronically on a low-threshold and cost-effective basis via a (tablet) computer or smartphone (electronically based MBI = eMBI). Indeed, online-based psychological interventions were found to reduce symptoms of anxiety and depression as well as suicidal thoughts [26–28].

## Methods

### Study design

The *mindmom* study is a bicentric prospective randomized controlled trial (RCT) with a repeated measures and crossed-lagged panel design. Participants will be equally allocated to one of the two study arms: “8-week eMBI course” (intervention group) or “Treatment as usual (TAU) alone” (control group). Both groups will be compared regarding superiority of an electronic mindfulness-based intervention over TAU. The study is being conducted at the University women’s hospitals of Heidelberg and Tübingen, Germany. Ethics approval has been obtained from both universities.

#### Objectives

This study aims to examine the clinical effectiveness and cost-effectiveness of an eMBI (*mindmom* app) within a sample of pregnant women during the third trimester of pregnancy who were screened positive for emotional distress.

The following content-related hypotheses will be examined:

Participation in the intervention leads to (a) decrease of symptoms of depression/anxiety or lowers prevalence of peripartum depression, (b) decrease of neuroendocrine stress markers, (c) increase of quality of life, (d) promotion of a more positive perception of the birth experience and attachment to the newborn, and (e) a reduction in the number of cesarean sections.

### Ethics

The study was approved by the ethics committee of the Medical Faculty of the University of Heidelberg on 7 January 2019 (S-744/2018), and recruitment of study participants started in February 2019. Any protocol modifications will be communicated immediately. It is conducted according to the international standards of the Declaration of Helsinki and subsequent amendments. The study is performed in compliance with the study protocol and with good clinical practice guidelines with the aim of protecting and preserving human rights. Gathering and processing of all personal data are subject to confidentiality and the European General Data Protection Regulation (EU-GDPR). This study will follow the CONSORT statement (Consolidated Standards of Reporting Trials, http://www.consort-statement.org) and the SPIRIT guidelines (Standard Protocol Items: Recommendations for Intervention Trials) (Additional file 1) [29]. The study was registered in the German Clinical Trials Registry (DRKS 00017210, study protocol version 3.0 of 18 December 2018).

### Study population, recruitment, and eligibility criteria

All pregnant women, attending routine pregnancy care in the state of Baden-Wuerttemberg from the 13th up to the 28th week of gestation, are invited to participate in a screening for mental distress according to the Edinburgh Postnatal Depression Scale (EPDS) by their local gynecologists. The screening is administered while attending prenatal care either at a registered gynecologist or one of the study sites. All questionnaires are digitally transmitted and evaluated at one of the study centers (University of Heidelberg, Germany, or University of Tübingen, Germany). Women with an EPDS score > 9 are offered an interdisciplinary medical-psychological assessment, since this EPDS cutoff indicates the presence of emotional distress.

The assessment is conducted by a psychologist from the study team, either in person or by video consultation by using the screening items of the Structured Clinical Interview for DSM-5 (SCID-5-CV) [30].

Women with an increased level of emotional distress (EPDS score > 9) are eligible for study participation if they are over 18 years of age, are under 29 weeks of gestation, have sufficient German language skills, and have internet access. As the state of Baden-Wuerttemberg, Germany, is the model region for this new type of care, potential study participants must be insured with one of the participating health insurance providers. After the psychological evaluation, one of the study physicians obtained informed consent for trial participation.

Women are not eligible for study participation if they are expecting multiples and have an otherwise increased risk of preterm delivery (e.g., preterm rupture of membranes) or if a serious fetal malformation has been diagnosed that might require a medical intervention immediately after birth. In addition, acute psychotic episodes or diagnosed schizophrenic disorders, suicidality, substance abuse disorders, borderline personality disorder, bipolar disorders, traumatic experiences without reference to the current pregnancy, or the need for an acute psychiatric treatment constitutes exclusion criteria. Study participants should not have participated in any MBI during the current pregnancy.

### Randomization

After informed consent is obtained, the participants are randomized 1:1 into the intervention (IG = eMBI) or control group (CG = TAU). The randomization list was generated by an independent scientific assistant using the R package “blockrand,” v. 1.3 (R v. 3.4.2, Rstudio v. 1.1.383). The group variable is blinded with a binary code (“0” and “1”) that was determined prior to the first assessment and is only known to the study staff and the app developers. The randomization list was recorded in writing and uploaded to the electronic case report form (eCRF) [31].

### Sample size

Estimation of sample size and power analysis were calculated with G*Power (Version 3.1.9.2) [32, 33]. The estimation was implemented for the confirmatory hypotheses, which aim for interaction between the between- (group) and within-subject factor (time of measurement), i.e., that the symptom burden develops differently in the two study groups over the course of time. The analysis with the lowest power is the two-factorial ANOVA with the outcome “PRAQ” (5 measurements, see Table 3, hypotheses 4–6).

The estimation is based on type 1 error of α = .016, Bonferroni-adjusted for 3 confirmatory analyses, and a power of 1 − β = .90. The statistically significant effect size is based on the results of a pilot study on mindfulness-based prevention in pregnant women with a history of depression [34]. Based on the mean values, standard deviations, and case numbers reported in this study, a final treatment effect of Cohen’s *d* = .34 (intervention group: *M* = 4.90, *SD* = 5.22, *n* = 21; control group: *M* = 6.62, *SD* = 4.94, *n* = 29) is calculated for the outcome “depressive symptoms” (EDPS score). According to Cohen (1988), this can be classified as a small effect size. Thus, the number of cases for the ANOVA design is estimated for small treatment effects (*f* = .10). Thus, *N* = 196 cases are needed to evaluate the eMBI. Assuming a dropout rate of 30%, the number of cases was determined to be *N* = 280 to reach a case number of *N* = 196 (*n* = 140 for each group or per region and *n* = 70 per group and region). With a sample size of *N* = 196, large- (*f* = .40) and medium-sized (*f* = .25) effects can be detected with a power of 1 − β = .99 and .98, respectively. Only small effects (*f* = .10) cannot be ruled out sufficiently with a power of 1 − β = .27 in case of non-significant between-subject effects.

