**Confirmative hypotheses**				
**1–3**	2 (group) × 7 (measurement)—ANOVA for repeated measures on the factor “measurement”	2	*F*-distribution	Group × measurement interaction effect
**4–6**	2 (group) × 5 (measurement)—ANOVA for repeated measures on the factor “measurement”	1	*F*-distribution	Group × measurement interaction effect

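### The planning effect f = .10 for the group × time interaction does not follow from the pilot's final d = .34, so the stated 90% power does not cover the pilot effect

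*Protocol article*

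**What the plan says.** The Sample size section says that sizing was done for the confirmatory hypotheses, "which aim for interaction between the between- (group) and within-subject factor (time of measurement"). Table 3 under Data analyses agrees: for all confirmatory tests the relevant effect is the "Group × measurement interaction effect".

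The error rates are given as follows: "The estimation is based on type 1 error of α = .016, Bonferroni-adjusted for 3 confirmatory analyses", "and a power of 1 − β = .90". The 5-visit PRAQ analysis is named as the one with the lowest power: "The analysis with the lowest power is the two-factorial ANOVA with the outcome “PRAQ” (5 measurements"). The other two confirmatory tests use seven visits: "2 (group) × 7 (measurement)—ANOVA for repeated measures on the factor “measurement". Table 2 schedules the EPDS at all seven visits, so the EPDS belongs to the 7-visit tests.

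The section says the effect size rests on a pilot study. It computes d = .34 from the final EPDS means of the two pilot arms, calls this small by conventional benchmarks, and then writes: "Thus, the number of cases for the ANOVA design is estimated for small treatment effects (*f* = .10"). From this come N = 196 evaluable women and, with 30% dropout, N = 280.

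**The concern.** Cohen's d = .34 is a difference between two groups at one time point. The f of a group × time interaction measures how much that difference varies over visits. Both may be called small, but that does not make them equal, and the section shows no conversion. If d = .34 implies an interaction f below .10, the trial has less than 90% power for the effect on which its planning is said to rest. A reader of the section would take it that a benefit of pilot size would be detected nine times in ten.

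**Working it through.** **Inputs from the Sample size section.** α = .016; power .90; 2 groups; 5 visits (PRAQ); N = 196; f = .10. Pilot arms: M 4.90, SD 5.22, n 21 against M 6.62, SD 4.94, n 29. Table 3 gives 7 visits for the other confirmatory tests.

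**Assumptions.** The correlation between visits (ρ) and the sphericity factor (ε) are not stated. I take ρ = .5 and ε = 1 because they reproduce the printed figures.

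**Step 1: the plan's own figures.**
- Pooled SD = √[(20·5.22² + 28·4.94²)/48] = 5.06; d = (6.62 − 4.90)/5.06 = .34, as stated.
- For the interaction in G*Power, λ = f²·N·m·ε/(1 − ρ), df1 = m − 1, df2 = (N − 2)(m − 1), with m visits. With f = .10 and m = 5, λ = .01·196·5/.5 = 19.6 and power is .904. The smallest even N reaching .90 is 194. N = 196 is reproduced.
- For between-subject effects, λ = f²·N·m/[1 + (m − 1)ρ]. At ρ = .5 power is .27 for f = .10 and .98 for f = .25, as printed. At ρ = .6 these would be .23 and .96, so the printed figures point to ρ = .5.
- G*Power's other two effect-size options would need N of 484 to 486 for f = .10. The f in the plan is therefore the one used here.
- 196/.7 = 280, as stated.

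**Step 2: from d to the interaction f.** Let D_t be the standardised group difference at visit t. With two equal groups, f = ½ · SD of D_t over visits (divisor m). Randomisation makes the expected difference at T1 zero.
- Linear, 5 visits (0, .085, .17, .255, .34): SD = .120, f = .060.
- Constant at .34 from T2, 5 visits: SD = .34·√(.2·.8) = .136, f = .068.
- Most favourable, 5 visits (0, 0, .34, .34, .34): SD = .34·√(.4·.6) = .167, f = .083.
- Linear, 7 visits: f = .057. Constant from T2: f = .060. Most favourable (three visits at 0, four at .34): f = .084.

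For any number of visits the ceiling is d/4 = .085. No pattern between 0 and .34 reaches .10. Linear divergence is a reference case and not a floor: 0, .17, .17, .17, .34 gives f = ½·√(2·.17²/5) = .054.

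**Step 3: power for d = .34 (α = .016, ε = 1).**

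| Test and pattern | f | N = 196, ρ = .5 | N = 196, ρ = .7 | N = 280, ρ = .5 |
|---|---|---|---|---|
| 5 visits, linear | .060 | .37 | .64 | .56 |
| 5 visits, constant from T2 | .068 | .49 | .79 | .70 |
| 5 visits, most favourable | .083 | .73 | .95 | .90 |
| 7 visits, linear | .057 | .40 | .70 | .60 |
| 7 visits, constant from T2 | .060 | .45 | .76 | .66 |
| 7 visits, most favourable | .084 | .85 | .99 | .97 |

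**Step 4: the final d that f = .10 stands for, 5 visits.** Linear: .34·.10/.0601 = .57. Most favourable: .34·.10/.0833 = .41.

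**The case against.** **No stated figure is miscalculated.** This is right. The value of d, N = 196, the between-subject powers and the dropout inflation all reproduce. The section attaches 90% to f = .10 and never prints 90% beside d = .34. A reader might infer that the sample size or the power figure is itself an arithmetic error, and the documents do not support that. What stands is a faulty inference from the pilot effect to f = .10.

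**f = .10 looks cautious, because d/2 = .17.** The value .17 is the f of a group contrast at a single visit, which is not the effect the confirmatory tests examine.

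**The shortfall depends on inputs that are not printed.** This stands in part. A higher true correlation raises power, and at ρ = .7 the most favourable patterns exceed .90. But at ρ = .7 only 118 women would be needed for f = .10, so the plan was not sized on that value. The intention-to-treat analysis with multiple imputation also keeps women with missing data, which puts the effective N between 196 and 280. The N = 280 column is an upper bound at ρ = .5, since imputation does not restore the lost information.

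**The unstated ρ and ε.** A journal article may leave software settings to the full protocol, so their absence is not a separate error.

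**The section already admits weak power for small effects.** It gives .27 for f = .10, but for between-subject effects. That caveat does not reach the confirmatory interaction.

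**Conclusion.** The point holds as a wrong derivation of the planning effect. The 90% power belongs to f = .10 in the 5-visit test, and that f is not the interaction effect implied by a final d = .34. Under the settings that reproduce N = 196, power for the pilot effect runs from linear divergence to the most favourable pattern as .37 to .73 for the 5-visit test (PRAQ). For the 7-visit tests, which include the EPDS measured in the pilot, it is .40 to .85. This rests on equal expected baselines, differences between 0 and .34, ρ = .5, ε = 1 and 196 complete cases. The 5-visit figures further assume that the EPDS effect carries over to the PRAQ, for which no pilot value is given.

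Two stronger readings should be avoided. A reader might turn d = .57 into EPDS points with the pilot's SD, but this trial selects women with EPDS above 9 and its SD is not given. A reader might also infer that a null result will be reported as absence of the pilot effect; no passage says so.

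**What to change.** Reword the Sample size section in three places.
- State that the 90% power applies to f = .10 in the 5-visit test with ρ = .5 and ε = 1, and that this corresponds to a final d of about .57 under linear divergence and at least .41 under the most favourable pattern.
- Remove the statement that f = .10 follows from the pilot's d = .34.
- Report power for d = .34 separately for the 5-visit and 7-visit tests over a range of ρ, for example .5 and .7 as in the table above. Do not convert to EPDS points.

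No extra patients are needed, and neither the tests nor the conduct of the trial changes. The cost is a less favourable stated power for an effect of pilot size.

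### The trial is planned in equal group-by-region cells, but the confirmatory ANOVAs leave out centre; adding it costs almost nothing and may gain a little power

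*Protocol article*

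**What the plan says.** The Study design section describes a trial at two university hospitals. The Sample size section divides the 280 women to be enrolled into 140 per group or per region and then "n* = 70 per group and region".

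Table 3 (Data analyses) gives the confirmatory tests in full. Hypotheses 1–3 use a group by seven-measurement ANOVA. Hypotheses 4–6 use an ANOVA written as "2 (group) × 5 (measurement"). In both, the group × measurement interaction is the only relevant effect. The Sample size section uses the same two-factor structure: "The analysis with the lowest power is the two-factorial ANOVA with the outcome" PRAQ. No centre or region term appears in the confirmatory rows, the exploratory rows or the multilevel model, which has only two levels, measurements and patients.

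On allocation, the Randomization section says "The randomization list was generated by an independent scientific assistant" with the R package blockrand. It gives a 1:1 ratio and names no stratification factor.

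**The concern.** The plan thinks in cells of group by region when it sets its numbers, then analyses the data as if region did not exist. If allocation was balanced within centre, the analysis should normally reflect that. Otherwise the error term contains variation that the design has already removed from the treatment comparison, and the test is conservative. If allocation was not balanced within centre, a centre term is still a cheap way to remove explainable variation.

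What is at stake is precision in the three confirmatory tests. Neither the validity of those tests nor the sample size is in question.

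**Working it through.** **1. Reproduce the plan's own figure.** Inputs from the Sample size section: "type 1 error of α = .016, Bonferroni-adjusted for 3 confirmatory analyses"; "a power of 1 − β = .90"; f = .10; k = 2 groups; m = 5 measurements. The correlation ρ among measurements and the sphericity factor ε are not stated; I assume ρ = .5 and ε = 1.

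- Noncentrality: λ = f²·N·m/(1 − ρ) = 0.01 × 196 × 5/0.5 = 19.6.
- Degrees of freedom: (k − 1)(m − 1) = 4 and (N − k)(m − 1) = 194 × 4 = 776.
- Power at N = 196: 0.904. The smallest even N with power of at least .90 is 194.
- 194/4 = 48.5, while 196/4 = 49, so 196 is the next number that fills four equal group-by-region cells.
- 196/0.70 = 280, 280/2 = 140 and 280/4 = 70, as stated.

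The plan's between-subject power figures support ρ = .5. There λ = f²·N·m/(1 + (m − 1)ρ). For f = .10 this is 0.01 × 980/3 = 3.27, with power 0.269 (stated .27). For f = .25 it is 0.0625 × 980/3 = 20.4, with power 0.981 (stated .98). Under other assumptions the minimum N would be 272 (ρ = .3), 118 (ρ = .7), 240 (ε = .75, ρ = .5) or 324 (ε = .5, ρ = .5).

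**2. Where centre enters the interaction test.** The group × measurement test uses each woman's deviations from her own mean. A centre difference that is the same at every visit is part of that mean and cancels. Only a centre-specific time course (centre × measurement) remains in the error term.

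**3. Add centre and centre × measurement.** The second degrees of freedom become (N − 3)(m − 1) = 193 × 4 = 772. Let R² be the share of the within-subject error that centre × measurement explains, an assumed range because the documents give none. Then λ = 19.6/(1 − R²).

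| R² (assumed) | λ | Power at N = 196 |
|---|---|---|
| 0 | 19.6 | 0.904 |
| 1% | 19.8 | 0.908 |
| 5% | 20.6 | 0.921 |
| 10% | 21.8 | 0.937 |

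With R² = 0 the minimum N stays 194. In the seven-measurement model the second degrees of freedom fall from 194 × 6 = 1164 to 193 × 6 = 1158.

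**4. Size of the conservatism if the list was stratified.** Leaving out the term widens the standard error by about 1/√(1 − R²): 0.5% at R² = 1%, 2.6% at 5% and 5.4% at 10%.

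**5. Chance split if the list was not stratified.** Suppose each region enrols 140 and 140 of 280 women go to the intervention. The intervention count in one region is then hypergeometric, with variance 140 × ½ × ½ × 140/279 = 17.6, SD 4.2 and a 95% range of 62–78 around 70.

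**The case against.** The strongest objection is that nothing here is an error. The unadjusted interaction test is valid, the sample size reproduces, and one app delivers both the intervention and the questionnaires, so centre-specific time courses may be small. With no such difference, power is 0.904 with or without centre. All of this stands, and it limits the point to an optional gain in precision.

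Four stronger readings are tempting but not supported:

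- **That allocation was not stratified by centre.** The Randomization section is silent in a condensed article, and blockrand can produce stratified lists. Silence does not show that stratification was omitted.
- **That the target of 70 per cell is a promise the design cannot keep.** It is a planning figure, 280 divided by 4. Separate lists would not guarantee it either, because 140 per region depends on recruitment.
- **That centre is confounded with group.** A chance split such as 62 against 78 does not bias a randomised comparison, and the standard error already reflects that variation.
- **That all centre variation inflates the error term.** A constant difference does not reach the interaction test. Nor do the documents give any source for a particular size of centre difference in change over time.

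Reading region as centre is also an inference. The eligibility section calls the whole federal state the model region. Two regions of 140 in a trial with two centres nevertheless make it the natural reading.

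**Conclusion.** The model point holds. The plan counts patients in group-by-region cells and fixes confirmatory models without centre. If allocation was balanced by centre, the group × measurement test is slightly conservative wherever time courses differ by centre. If it was not, the test is valid and some precision is lost. In neither case does the omission inflate the type I error, and the stated N is not wrong.

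The gain is small: power moves from 0.904 to between 0.908 and 0.937 for an assumed R² of 1–10%, and does not move if time courses are alike. These figures rest on ρ = .5, sphericity and N = 196 evaluable women. This is a free improvement with a small gain.

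**What to change.** Add centre and centre × measurement to the confirmatory ANOVAs in Table 3, in a dated amendment made before any unblinded analysis, so that the choice cannot look data-driven. The planned imputation uses all variables of the analysis model, so centre should enter it as well.

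Report whether the existing blockrand list was stratified by centre. The list has already been generated and recruitment has started, so the text should say what was done and should not assert stratification unless that is so.

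Cost: one between-subject degree of freedom, plus 4 within-subject error degrees of freedom in the five-measurement model or 6 in the seven-measurement models. No additional patients or data are needed.
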